#### Biomechanics

Eight Motion Analysis cameras (Motion Analysis Corp., Santa Rosa, CA) sampling at 240 Hz will record the 3D trajectories of retroreflective markers placed over the participants most symptomatic limb as they walk along a 20 m runway. A force platform (Kistler AG, Winterthur, Switzerland) will collect ground reaction force data at a frequency of 2400 Hz as the participant walks along the runway. This will be done for 5 successful trials in each of 3 footwear conditions for each participant: (1) participant’s own shoe (baseline condition), (2) participant’s own shoe with the lateral wedge insole, and (3) participant’s own shoe with the medial wedge insole. A successful trial is defined as one where the participant lands with their most symptomatic limb near the center of the force platform, does not touch the force platform with their other limb, and maintains a gait speed of 1.3 ± 0.07 m/s as measured by two photocells.

Kinetic and kinematic data will be filtered using 4^th^ order Butterworth low-pass filters with cut-off frequencies of 50 Hz and 12 Hz, respectively. KAMs during stance will be calculated using an inverse dynamics approach, and the peak KAM (first peak) will be identified for each trial [4, 19]. The average KAM across trials for each footwear condition will then be calculated and represented as a percent change from the baseline condition value. The KAM impulse (integral of KAMs with respect to time) and Varus thrust (maximum mediolateral displacement of knee joint center from touchdown) [24] and the KAM impulse (integral of KAMs with respect to time) [25] will also be calculated as these variables have also been shown to be related to knee OA [6, 24]. At the baseline visit, biomechanical testing and DXA scans will be performed and survey information will be collected. After determining the peak KAMs for all three conditions, the percent change in KAM will be determined for the medial and lateral wedge conditions.

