#### Comfort

Some studies have suggested that footwear comfort may be an important variable in determining the effectiveness of a footwear intervention on pain management [40]. Therefore, we will administer a paper-based 100 mm visual analog scale with the terms “extremely comfortable” and “extremely uncomfortable” as anchors at 100 mm and 0 mm, respectively. The tests will be administered on paper at baseline.

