### Randomization

Following the baseline laboratory and survey testing, participants will be randomized into one of two study arms: (1) a KAM-reduction experimental group (KAM-R), or (2) a waitlist control group. In the KAM-R group, participants will be given either a medial or lateral wedge insole (whichever insole reduces KAMs more for each individual participant) to put inside their own shoe and use for 3 months. In the waitlist control group, participants will be asked to continue using their own shoes for a period of 3 months, and following this will be provided with access to a wedged insole (whichever reduces KAMs more based on baseline data collection).

Participants will be randomized using a multi-block-randomization procedure into either the KAM-R or waitlist control group. Specifically, a separate block sequence will be used for males and females to ensure an even sex distribution across groups. A block size of 6 will be used for each, and the sequence will be determined from a random number generator.

The one exception to this block randomization procedure is that if neither wedged insole produces a KAM reduction, the participant will be excluded from the main study altogether. This scenario will not be common, as most people do experience a large change in KAMs with one of the two wedged insole types, but this strategy will ensure that all participants in the KAM-R and waitlist control groups are all biomechanically suitable for a wedged insole intervention. Thus, neither group will contain biomechanical non-responders to wedged insoles.

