### Blinding

Knowledge of the participant’s KAM change is required to ensure that the study sample consists entirely of those who experience a reduction in KAMs with at least one insole type. We will randomize patients to either the KAM-R or control group prior to knowing the KAM results and prior to any data collection. After collecting biomechanical data, KAM results will be assessed to verify that the participant experienced a KAM reduction in at least one wedged insole type. As described previously, in cases where the participant does not experience a KAM reduction with either insole, they will be excluded from the main study. Thus our knowledge of KAM changes will not affect our initial randomization, and only be used as a verification tool. Although researchers will be aware of each participant’s study group following randomization (in order to assign the participants in the KAM-R group an insole to take home), the researchers will be blinded during future survey data collection and data analysis as identifying information will be stripped by an independent researcher and replaced with unique patient ID numbers and numerical values for group allocation. Those involved in statistical analysis will be blinded to the group allocation and outcomes during data analysis. All KAM-R participants will be aware as to which condition they have been assigned, based on knowing that they have received an insole. All control condition participants will be aware that they have not received an insole at baseline, but will receive an insole at 3 months. Thus, the study will not be blinded at baseline data collection; however, follow-up data collection and data analysis will be blinded to the researchers.

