#### Within group analyses

All data will be analyzed on an intention to treat basis. Changes from baseline to 3 months will be assessed within groups for ordinal data (UCLA score) using Wilcoxon Signed Rank test (α = 0.05). KOOS subsection scores and PASE scores will be compared between baseline and at 3 months using paired-samples t-tests (α = 0.05). KAMs, KAM impulse, varus thrust, and footwear comfort will be compared between the neutral shoe and assigned wedged insole condition at baseline for the KAM-R group using paired-samples t-tests (α = 0.05). All tests will be two-tailed, except in the case of KAMs and KAM impulse, where one-tailed tests will be used. The reason for this is that KAM reduction is strictly controlled in this study and so KAM and KAM impulse reductions are the only possible outcome.

A multivariable linear regression (α = 0.05) will also be conducted on the KAM-R group to evaluate whether KAM reduction, KAM impulse, varus thrust and footwear comfort can predict change in pain over 3 months. Covariates tested in these four models will include adiposity and Kellgren-Lawrence grade.

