#### Between group analyses

Ordinal data from UCLA scores and Kellgren-Lawrence grades will be compared at baseline and at 3 months (UCLA score only) between the control and KAM-R group using Mann–Whitney U tests (α = 0.05). KOOS subsection scores, PASE scores, KAMs, KAM impulse, varus thrust, adiposity, footwear comfort, and adherence will be compared at baseline between the KAM-R and control group using a MANOVA test (α = 0.05) with independent-samples t-tests for post-hoc analysis. Changes over 3 months will also be assessed between groups using a MANOVA (α = 0.05) with independent-samples t-tests for post-hoc analysis. All tests will be two-tailed, except in the case of KAMs and KAM impulse, where one-tailed tests will be used. The reason for this is that KAM reduction is strictly controlled in this study and so a reduction in KAMs and KAM impulse is the only possible outcome. It should be noted that all between group comparisons are exploratory analyses, as we may not be powered to detect any significant differences between groups.

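### The baseline own-shoe versus wedge tests of KAM impulse and varus thrust use the KAM-R arm only, although the same contrast exists in the controls; the test is valid but loses precision

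*Protocol article*

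**What the plan says.** All places are in the protocol article.

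- **Within group analyses** names four variables (KAMs, KAM impulse, varus thrust and footwear comfort), which "will be compared between the neutral shoe and assigned wedged insole condition at baseline for the KAM-R group using paired-samples t-tests". The paired t-tests are thus limited to the KAM-R arm. Tests are two-tailed, except those on KAMs and KAM impulse, which are one-tailed.
- **Biomechanics** describes the baseline gait test in own shoe, lateral wedge and medial wedge: "This will be done for 5 successful trials in each of 3 footwear conditions for each participant". No arm is exempt.
- **Randomization** gives KAM-R participants one of the two wedges, "whichever insole reduces KAMs more for each individual participant". Controls get theirs after the three-month wait: "whichever reduces KAMs more based on baseline data collection". Anyone whose KAM falls with neither wedge leaves the main study, whichever the arm.
- **Comfort** says of the visual analogue scale only this: "The tests will be administered on paper at baseline". It does not say which footwear conditions are rated, or whether controls rate a wedge.
- **Between group analyses** uses the controls' baseline values for another purpose: "KAMs, KAM impulse, varus thrust, adiposity, footwear comfort, and adherence will be compared at baseline between the KAM-R and control group".

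**The concern.** The comparison of own shoe with the chosen wedge is made within each person at one visit, before any insole is worn at home. Treatment cannot alter it. The choice rule and the eligibility filter are the same in both arms, so the contrast means the same thing in a control as in a KAM-R participant. The plan gives no reason for leaving the controls out.

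The article presents the wedge as a means to a mechanical end, and these tests show what the individually chosen wedge does mechanically. Peak KAM says little here, because the wedge is chosen on it. Varus thrust is not used in the choice, and KAM impulse is not used directly, so these two tests carry most of the information. Both are listed as secondary outcomes. With half the pairs, the estimates are less precise and a modest effect is more likely to be missed.

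**Working it through.** **1. Is the contrast available in the controls?**

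| Element | KAM-R | Control | Section |
|---|---|---|---|
| Walks in all three conditions at baseline | yes | yes | Biomechanics |
| Wedge chosen by larger KAM reduction | yes | yes, for later use | Randomization |
| Excluded if neither wedge reduces KAM | yes | yes | Randomization, Blinding |
| Comfort rated in the wedge | implied by the planned test | not stated | Comfort, Within group analyses |

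It is available and identically defined for KAM impulse and varus thrust. For comfort this is not established.

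**2. Numbers of pairs.** Sample size calculation gives 20 per group, 40 in total, and 46 recruited, from a difference of 13.4 points, SD 15, 80% power and α = 0.05. The 20 reproduces as 2 × (1.960 + 0.842)² × 15² / 13.4² = 19.7, rounded up to 20. The 46 reproduces as 40 × 1.15. These figures concern KOOS pain. The article gives no effect size or SD for the gait contrasts, so the results below are in units of the SD of the paired difference. The gait data are complete at baseline, before dropout, so 23 v 46 is the natural comparison. It assumes 1:1 allocation (the ratio is not stated, but 20 per group implies it) and 46 main-study participants with usable gait data.

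**3. Precision.** The 95% half-width is t(0.975, n−1)/√n.

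- n = 23: 2.074/4.796 = 0.432
- n = 46: 2.014/6.782 = 0.297

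The interval is 1 − 0.297/0.432 = 31% narrower. The standard error falls by a factor of √(46/23) = 1.41. With the post-dropout counts, 20 v 40, the half-widths are 0.468 and 0.320.

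**4. Power.** This is the probability that a noncentral t variable with n−1 degrees of freedom and noncentrality d√n exceeds the critical value. The critical value is t(0.975, n−1) two-tailed (varus thrust) and t(0.95, n−1) one-tailed (KAM impulse, as the plan specifies). The values of d are assumed.

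| Assumed d | Two-tailed, n = 23 | n = 46 | One-tailed, n = 23 | n = 46 |
|---|---|---|---|---|
| 0.3 | 0.280 | 0.512 | 0.401 | 0.640 |
| 0.4 | 0.450 | 0.756 | 0.585 | 0.848 |
| 0.5 | 0.630 | 0.913 | 0.751 | 0.955 |
| 0.6 | 0.785 | 0.978 | 0.873 | 0.991 |

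The difference detectable with 80% power falls from 0.61 to 0.42 SD two-tailed, and from 0.54 to 0.37 SD one-tailed.

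**The case against.** The strongest defence is that this is a choice of analysis set and not an error. The test stands among the within-group analyses and concerns the wedge actually assigned. It describes the mechanical change in the people who go on to wear the insole, and it matches the sample of the regression. It is unbiased for that purpose. All of this stands, and it is why the KAM-R result should be kept. It does not explain why the more precise estimate from the same visit should not stand beside it.

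Three stronger readings are tempting, and the article does not support them.

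- *Half the data are discarded.* The controls' gait data serve the eligibility check ("KAM results will be assessed to verify that the participant experienced a KAM reduction in at least one wedged insole type"), the choice of their later insole and the baseline between-group comparison. What goes unused is their own-shoe versus wedge contrast in these tests.
- *Comfort can be pooled in the same way.* Walking in a wedge is not rating it, and the Comfort section does not say that controls do so. Randomization also places allocation after baseline testing, while Blinding places it before any data collection. If participants know their arm when they rate, comfort may differ by arm.
- *Peak KAM suffers equally.* It has the same restriction, but it falls by construction because the wedge is chosen on it. Adding controls would not cure that, so pooling adds little.

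It is also fair to object that the power figures rest on assumed effects, and that KAM impulse loses less than a two-tailed calculation would suggest. The table above allows for the second point, and the half-width result needs no assumed effect.

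**Conclusion.** The point holds for KAM impulse and varus thrust as an avoidable loss of precision on secondary outcomes. About half of the available pairs (23 of 46) are left out, which makes the 95% interval wider than it need be: a half-width of 0.43 instead of 0.30 SD. At an assumed change of 0.5 SD, power is 0.63 instead of 0.91 for varus thrust, and 0.75 instead of 0.96 for KAM impulse.

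A reader might infer that the planned test is invalid, or that the trial's main result is weakened. Neither follows. The restricted test is sound, KOOS pain is untouched, and the regression uses individual KAM-R values and does not depend on these t-tests.

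The size rests on 1:1 allocation, no loss of baseline gait data, and standardised changes chosen for illustration.

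**What to change.** In Within group analyses:

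1. Run the own-shoe versus KAM-reducing-wedge comparisons of KAM impulse and varus thrust on all main-study participants from both arms. For controls, use the wedge already identified at baseline.
2. Report the KAM-R arm alone as a secondary line.
3. State whether controls rate comfort in the wedge at baseline. Pool comfort only if they do, and show it by arm as well. Reconcile Randomization and Blinding on whether allocation comes before or after baseline testing.
4. Leave peak KAM as a description of the selected wedge.

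For KAM impulse and varus thrust the cost is analysis wording only. The planned baseline visit already yields the data, so no new measurement, visit or participant burden is needed.

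### Peak KAM is tested on the same baseline trials that chose the insole and removed non-reducers, so its p-value carries no information; the certainty claimed for KAM impulse is untrue

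*Protocol article*

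**What the plan says.** Under Biomechanics, each participant walks five successful trials in each of three conditions (own shoe, lateral wedge, medial wedge) at the baseline visit. The selection variable is the first peak: "KAMs during stance will be calculated using an inverse dynamics approach, and the peak KAM (first peak) will be identified for each trial". Trials are averaged by condition and expressed as percent change from own shoe. KAM impulse, the time integral, is calculated as a separate variable.

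Under Randomization, the KAM-R participant receives "whichever insole reduces KAMs more for each individual participant", and "if neither wedged insole produces a KAM reduction, the participant will be excluded from the main study altogether". The Blinding section repeats the exclusion.

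Under Within group analyses, "KAMs, KAM impulse, varus thrust, and footwear comfort will be compared between the neutral shoe and assigned wedged insole condition at baseline" by paired t-tests at α = 0.05 in the KAM-R group. Tests are two-tailed "except in the case of KAMs and KAM impulse, where one-tailed tests will be used". The reason given is "KAM reduction is strictly controlled in this study and so KAM and KAM impulse reductions are the only possible outcome".

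Under Between group analyses, KAMs and KAM impulse are among the variables compared between arms at baseline. They are again one-tailed, because "KAM reduction is strictly controlled in this study and so a reduction in KAMs and KAM impulse is the only possible outcome".

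The Abstract says that the surveys are repeated at 3 months. No repeat gait test is described.

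**The concern.** A test of whether KAM fell is informative only if the data could have shown that it did not. Here the lower of two measured insole values is taken and participants without a measured fall are removed. The surviving differences are then tested on the same trials. The plan's own reason for using one tail concedes that the result is settled in advance.

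Three things are at stake:

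- **Peak KAM p-value.** It would be reported as evidence that the mechanism was delivered, and it is not evidence.
- **Size of the reduction.** Choosing the best of several noisy means and truncating at zero makes the reported mean too large.
- **KAM impulse.** The plan treats it as controlled when only the first peak is. The Background links KAM impulse to cartilage loss, so a rise in impulse would matter.

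The protocol argues in its Background and Discussion that every KAM-R participant truly has reduced KAMs, and this comparison is its direct support for that.

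**Working it through.** **Inputs from the protocol.** Five trials per condition, three conditions, one visit. Insole chosen by lower mean peak KAM. Participants with no reduction are excluded. Paired t-test at α = 0.05, one-tailed. Group size 20. The plan computes no figure for KAM. Its sample size section supplies the n, which reproduces as 2 × (1.960 + 0.842)² × 15² / 13.4² = 19.67, so 20.

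**Step 1: how many qualify if wedges do nothing.** The own-shoe, lateral and medial means are then exchangeable. A participant is excluded only if own shoe is the lowest of the three, with probability 1/3. So 1 − 1/3 = 67% show a reduction by chance. Simulation gives 67%.

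**Step 2: the peak KAM test with no true effect.** The analysed difference is min(lateral, medial) − own shoe, kept only if below 0. In 20,000 simulated trials:

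| n | one-tailed rejection | two-tailed rejection |
|---|---|---|
| 20 | 100% | 100% |
| 23 | 100% | 100% |

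The apparent mean reduction is 0.90 SD of a single insole-minus-shoe change. None of this depends on the size of the measurement error.

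**Step 3: size of the overstatement.** This needs a trial-to-trial SD, s, which the protocol does not give. Assume mean effects of −5% (one wedge) and +5% (the other) and a between-patient SD of 5%. The error variance of a change is 2s²/5, and its share of the total is (2s²/5) / (2s²/5 + 25).

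| Trial SD (assumed) | Error share | Reported reduction | True reduction | Excess (points) | Accepted with no true reduction |
|---|---|---|---|---|---|
| 10% | 62% | 8.6% | 5.9% | 2.7 | 11% |
| 5% | 29% | 7.0% | 6.3% | 0.7 | 6% |
| 3% | 13% | 6.6% | 6.4% | 0.2 | 4% |

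A second scaling uses the 15–43% of patients that the Background says respond opposite to the group average. That sets the mean effect at 1.04 to 0.18 SD of the observed change. The relative overstatement is then about 3–8% if error is 10% of the variance of change, 7–25% at 25%, and 14–71% at 50%.

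**Step 4: KAM impulse with no true effect.** The peak–impulse correlation is not in the protocol, so it is varied (n = 20, one-tailed).

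| Correlation (assumed) | Rejection | Selected participants whose impulse does not fall |
|---|---|---|
| 0 | 5.1% | 50% |
| 0.3 | 32% | 39% |
| 0.5 | 68% | 31% |
| 0.7 | 95% | 23% |
| 0.9 | 100% | 12% |

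With true effects the point remains. If peak and impulse changes both average −4 to −6 with SD 5 and correlate 0.5–0.8, impulse rises in about 6–15% of participants whose peak falls.

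**Step 5: the between-arm comparison.** The exclusion rule applies to both arms. At baseline, randomisation gives no reason to expect KAM to be lower in one arm. The control of KAM cited for one tail concerns insole against own shoe within a participant, not arm against arm.

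**The case against.** - **These are secondary outcomes.** True. The primary outcome is KOOS pain and its test does not use KAM. The plan also labels all between-group comparisons exploratory, and the Blinding section calls KAM knowledge a verification tool. This limits the weight of the point but does not make the peak KAM test informative.
- **The bias may be trivial.** This stands. At a trial SD of 3% the excess is 0.2 points. Only its direction is certain, given any trial-to-trial error.
- **A pre-specified one-tailed test is not invalid in itself.** This stands for impulse: with zero correlation the error rate is 5.1%. What fails is the reason given. Inflation follows only so far as impulse correlates with the selected peak, which is likely because both come from the same moment curve.
- **The between-arm limb rests on a reading.** In part. The section does not say which footwear condition is compared, and the sentence on 3-month changes does not list KAM. The baseline comparison does list KAMs and KAM impulse, and the one-tailed reason is stated there.

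A reader might infer more than the documents support:

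- **That the single tail is the fault for peak KAM.** It is not. A two-tailed test on the same data also rejects in 100% of null trials.
- **That a harmful change in impulse would go unseen.** The plan promises descriptive analyses of all variables. A mean rise would be visible; it could not be declared significant.
- **That the regression of pain change on KAM reduction is shown to be biased.** A constant shift in a predictor leaves its slope unchanged, and no distortion of the slope has been demonstrated here.

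**Conclusion.** The point holds in this form and should be corrected; it does not threaten the primary analysis. For peak KAM, the circularity follows from the protocol's own steps and needs no assumed value: the null is rejected in 100% of simulated trials with either tail, and the p-value should not be reported as evidence. The mean reduction is biased upward, by 2.7 down to 0.2 percentage points over the assumed trial SDs of 10% to 3%, so no single figure can be claimed. For KAM impulse, the statement that a fall is bound to occur is false because impulse enters neither the choice nor the exclusion. How far its error rate is inflated depends on an assumed correlation. The one-tailed rule in the between-arm section has no basis at baseline.

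**What to change.** Keep the prescription rule, and change the analysis as follows.

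1. **Peak KAM, within group.** Drop the hypothesis test. Report the change descriptively and state that it was measured on the data used for selection.
2. **If an unbiased estimate is wanted.** Cross-validate over all participants who had gait testing, including those excluded. In each fold, apply both the insole choice and the exclusion rule to the training trials, and evaluate only the held-out own-shoe and insole trials. Use a participant-level bootstrap for the confidence interval.
3. **KAM impulse.** Report it two-sided on the same cross-validated basis, or descriptively with the share of participants whose impulse rises. Delete the claim that a reduction is certain.
4. **Between group analyses.** Make any KAM or impulse comparison two-sided.

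Re-choosing the insole by leave-one-trial-out among retained participants only is not enough, because they were already filtered on all five trials. In simulation that still rejects in about 80% of null trials, and at a trial SD of 10% it gives −7.8% against a true −5.9% (uncorrected −8.6%). Re-applying both rules over everyone tested gives about 5% and −5.8%.

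The cost is some analysis code on trials already collected, and a smaller, slightly less precise reported KAM reduction.

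### In the KAM-R group, peak KAM is tested on the walks that selected for a reduction, and KAM impulse, which was never screened, is wrongly said to be unable to rise

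*Protocol article*

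**What the plan says.** The Biomechanics section describes one gait session, at baseline: "This will be done for 5 successful trials in each of 3 footwear conditions for each participant" (own shoe, lateral wedge, medial wedge). Within it, "the peak KAM (first peak) will be identified for each trial". The peaks are averaged by condition and expressed as percent change from own shoe. KAM impulse, the time integral of the KAM curve, is calculated as a separate variable.

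Under Randomization, the KAM-R group receives "whichever insole reduces KAMs more for each individual participant", and a participant in whom neither wedge lowers KAM leaves the main study. The Blinding section confirms that, after the gait data are collected, "KAM results will be assessed to verify that the participant experienced a KAM reduction in at least one wedged insole type".

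Within group analyses then sets out the test: "KAMs, KAM impulse, varus thrust, and footwear comfort will be compared between the neutral shoe and assigned wedged insole condition at baseline", in the KAM-R group, by paired t-tests at 0.05. On sidedness it says "All tests will be two-tailed, except in the case of KAMs and KAM impulse, where one-tailed tests will be used". The reason given is that "KAM reduction is strictly controlled in this study and so KAM and KAM impulse reductions are the only possible outcome". Between group analyses repeats both the one-tailed rule and its reason in almost the same words.

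The Abstract has only the surveys repeated at 3 months. No second gait session is described.

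**The concern.** Two different faults sit in one sentence.

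- **Peak KAM.** The data that decide which wedge is assigned, and who stays in, are the data then tested. The entry rule removes the null hypothesis before the test is run.
- **KAM impulse.** The choice and the exclusion use the peak. Nothing in the rule constrains the integral, so the stated ground for a one-tailed test is missing.

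The trial's stated purpose is to learn what reduced KAMs do to pain and function, and this is the only own-shoe against assigned-wedge comparison in the plan. Readers will take from it how much load was removed. A p-value that comes out significant whether or not the wedges work cannot support that, and a mean difference chosen for being large will be too large. The Background links KAM impulse to cartilage loss over 12 months, so a rise in impulse is a result that the plan should be able to report.

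**Working it through.** **Inputs from the article.** Five walks in each of three conditions; selection on percent change in first-peak KAM; the better wedge assigned; non-reducers excluded; α = 0.05, one-tailed. The plan gives no figure of its own for these tests. The group size comes from the Sample size section: 20 per group, or 46/2 = 23 with the dropout allowance. The 20 reproduces as 2 × [15 × (1.960 + 0.842)/13.4]² = 19.67, rounded up. It is used here only to fix n.

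**Inputs assumed.** Normal walk error, independent between conditions, and no true effect of either wedge on anyone. The correlation ρ between peak and impulse error is not given, so it is varied from 0 to 0.9.

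**Step 1: peak KAM, what selection alone does.** Let the three condition means have error SD σ and the same true value.
- A participant passes the screen unless own shoe happens to be the lowest of the three, so the pass rate is 1 − 1/3 = 0.667. The simulation gave 0.67.
- The analysed difference is the lowest of three values minus own shoe. The expected minimum of three standard normals is −3/(2√π) = −0.846. Dividing by the pass rate gives −0.846/0.667 = −1.27σ. The simulation gave −0.567 in units of the single-walk SD, and −0.567 × √5 = −1.27σ.
- All retained differences are below zero. Over 8,000 simulated trials the paired t-test rejected in 100%, at n = 20 and n = 23, one-tailed and two-tailed.

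Useless insoles would therefore still produce an apparent mean reduction of 1.27σ and a significant test. If σ were 2% to 4% of KAM (assumed), that is 2.5% to 5.1%.

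**Step 2: KAM impulse, can it rise?** In the same simulation, the share of retained participants whose impulse is higher with the assigned wedge was 50% at ρ = 0, 31% at ρ = 0.5 and 12% at ρ = 0.9. A reduction is not the only possible outcome.

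**Step 3: KAM impulse, size of the test (n = 20, nominal 0.05).**

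| ρ (assumed) | One-tailed | Two-tailed |
|---|---|---|
| 0 | 0.05 | 0.05 |
| 0.3 | 0.33 | 0.22 |
| 0.5 | 0.68 | 0.54 |
| 0.7 | 0.94 | 0.89 |
| 0.9 | 1.00 | 1.00 |

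Impulse is the integral of the same curve on the same walks, so some positive correlation is to be expected. Changing the tail alone does not restore the size.

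**Step 4: would splitting the walks rescue the test?** Select on walks 1, 3 and 5, test on walks 2 and 4, with no true effect, one-tailed 5%.
- Rule applied to everyone tested, including those the trial excludes: rejection about 0.05.
- Enrolled participants only, three-walk rule re-applied: 0.28 to 0.31. About 16% are dropped, and about 19% of those kept are analysed on a wedge that they were not given.
- Enrolled participants only, wedge actually assigned: 0.88 to 0.92, with the mean reduction still 1.27σ.

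The enrolled cohort has already been selected on all five walks, so its held-out walks are not independent of the selection.

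**The case against.** **The plan is open about it.** It says that a reduction is guaranteed by design, so a careful reader would not take the peak-KAM p-value for a discovery, and descriptive analyses of all variables are already planned. That is fair, and it argues for dropping the test. It does not deal with the overstated mean.

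**Complete absence of effect is an extreme case.** The Background reports that lateral wedges lower KAM on average, and Randomization expects a large change with one wedge in most people. This stands. A reader might infer from the 100% rejection rate that the reductions are an artefact. The documents do not support that. A true reduction may well exist; the point is that this test cannot show it and that its size is overstated.

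**The one-tailed test might be blamed for both p-values.** That reading is also too strong. For peak KAM the fault is selection, and a two-tailed test fails equally. For impulse, a pre-specified one-tailed test keeps its 5% size if impulse error is independent of peak error. The tail only prevents a rise from being declared. Any distortion of the p-value comes from correlated error, and its size rests on a ρ that the article does not give.

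**These outcomes are secondary.** They serve as a check that the intervention did what was intended. A reader might extend the fault to the pain result, but the KOOS pain comparison and the sample size calculation do not use these tests.

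**Conclusion.** The point holds, as a correction that should be made to secondary analyses.

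- **Peak KAM:** the significance test carries no information, because its outcome is fixed by the choice and exclusion rules. The 100% rejection under no effect does not depend on the walk error. The overstatement of the mean does, and it cannot be sized from the article.
- **KAM impulse:** the statement that only a reduction is possible is wrong, because the article calculates the screening percent change from peak KAM. This rests on reading KAMs in the Randomization rule as peak KAM, which the Biomechanics section supports. The one-tailed rule therefore has no basis, and the test is exposed to selection bias of unknown size: none at ρ = 0, severe at ρ of 0.5 or more.

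**What to change.** In Within group analyses:
- Delete the significance test of peak KAM. Report the reduction descriptively as the selected dose, and state that it is inflated by selection on the same walks.
- Make the impulse comparison two-tailed, report it as an estimate with a confidence interval, and state that it is subject to selection on peak KAM.

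In Within group analyses and Between group analyses:
- Delete the claim that a reduction in KAM impulse is the only possible outcome, and the one-tailed rule that rests on it.

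Split-walk inference should be offered only if the choose-and-verify rule is applied to the selection walks of everyone tested, including those whom the trial excludes. It then estimates the effect of the selection rule, not of the insole that each enrolled participant wore. It should not be run on the enrolled cohort alone.

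The cost is wording only, with no new patients, visits or measurements. The trial loses a p-value, and the stated KAM reduction carries a caveat.
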